## Abstract

**Background:**

Exercise-induced laryngeal obstruction (EILO) is a common cause of exertional breathing problems in young individuals, caused by paradoxical inspiratory adduction of laryngeal structures, and diagnosed by continuous visualization of the larynx during high-intensity exercise. Empirical data suggest that EILO consists of different subtypes, possibly requiring different therapeutic approaches. Currently applied treatments do not rest on randomized controlled trials, and international guidelines based on good evidence can therefore not be established. This study aims to provide evidence-based information on treatment schemes commonly applied in patients with EILO.

**Methods and Analysis:**

Consenting patients consecutively diagnosed with EILO at Haukeland University Hospital will be randomized into four non-invasive treatment arms, based on promising reports from non-randomized studies: (A) standardized information and breathing advice only (IBA), (B) IBA plus inspiratory muscle training, (C) IBA plus speech therapy, and (D) IBA plus inspiratory muscle training and speech therapy. Differential effects in predefined EILO subtypes will be addressed. Patients failing the non-invasive approach and otherwise qualifying for surgical treatment by current department policy will be considered for randomization into (E) standard or (F) minimally invasive laser supraglottoplasty or (G) no surgery. Power calculations are based on the main outcomes, laryngeal adduction during peak exercise, rated by a validated scoring system before and after the interventions.

**Ethics and Dissemination:**

The study will assess approaches to EILO treatments that despite widespread use, are insufficiently tested in structured, verifiable, randomized, controlled studies, and is therefore considered ethically sound. The study will provide knowledge listed as a priority in a recent statement issued by the European Respiratory Society, requested by clinicians and researchers engaged in this area, and relevant to 5–7% of young people. Dissemination will occur in peer-reviewed journals, at relevant media platforms and conferences, and by engaging with patient organizations and the healthcare bureaucracy.

## Introduction

Paradoxical closure of the larynx during physical exertion, or exercise-induced laryngeal obstruction (EILO), has now been recognized as a relatively common cause of exertional breathing problems in particularly young and physically active individuals. Studies report prevalence rates of 5–7% in unselected adolescent populations (1, 2), and even higher in groups where exercise is particularly important (3, 4). EILO hampers participation in physical activity, and can in severe cases lead to disabling exercise-related dyspnoea. Diagnostic confusion between EILO and exercise-induced asthma likely leads to overuse of asthma medication and underuse of EILO treatment (5–8).

Laryngeal function during exercise is not fully understood, which hampers our approach to the treatment of EILO. Empirical data suggest that EILO consists of different subtypes that might require different therapeutic approaches. However, despite several studies suggesting positive treatment responses, widely applied therapeutic approaches still do not rest on randomized controlled trials (9–14). Randomized clinical trials (RCT) are pivotal in guiding clinical practice, and valid diagnostic methods and outcome measures are vital for their applicability (15). No RCTs have in fact been performed in this area, and it was therefore challenging to decide where to focus our efforts. We have designed a trial that will answer questions we find imperative and involves treatments used in our own department based on accumulated clinical experience. The overarching aim of this study is to provide evidence-based information on interventions commonly applied to treat EILO.

### EILO Diagnostic Methods and Graded Outcome Measures

EILO is diagnosed by laryngoscopy performed continuously from rest to peak exercise, a test labeled continuous laryngoscopy exercise (CLE) test (13, 16, 17). The test provides visualization of the level of the obstruction within the larynx; i.e., glottic, supraglottic (or both), and epiglottic obstruction (Figure 1), and permits timing of the events; i.e., what laryngeal structure that incites the adduction. By definition, EILO is inappropriate inspiratory laryngeal adduction that occurs during ongoing exercise in a larynx that appears normal while at rest (13). The CLE scores assess *the relative* degree of inspiratory adduction of the supraglottic and vocal fold during increasing exercise (18). As CLE scores rest on judgements made by raters, there is inevitably an aspect of subjectivity involved when rating of EILO is performed. Studies addressing the validity of this CLE scoring system have reached somewhat variable conclusions (18–20). It is reasonable to conclude from the literature that experience is a key factor that influences the repeatability of the rater. Although the CLE scoring system has its shortcomings, it is to date the most objective measure of EILO severity, and it is regularly used in everyday clinics worldwide.

**Figure 1 F1:**
[figure not shown]
Laryngeal anatomy with relevant landmarks as seen through a laryngoscope.

Our group recently published results showing that translaryngeal pressure measurements performed throughout the CLE test is a feasible procedure in healthy volunteers. Combined with flow measurements obtained by the mouth, translaryngeal resistance is a promising objective numerical measure that can be used in the evaluation of patients with EILO (21). Objective numerical measures are of particular interest in cases where supraglottoplasty is considered, as surgery is an irreversible procedure involving (as all surgery) aspects of risk. As surgery leaves obvious marks in the larynx, blinding of raters will not be possible in research. Therefore, objective measures of resistance is highly welcomed.

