### The Specific Aim of This Study

The specific aim of this study is to test the effect of four different non-invasive treatment approaches in a randomized controlled design in patients consecutively diagnosed with EILO at Haukeland University Hospital. Due to financial reasons, this is a one-center only study. Findings from continuous laryngoscopy performed during maximal treadmill exercise (CLE) will be used to diagnose and subtype EILO, and CLE-scores will be used to assess changes in the larynx at peak exercise before vs. after the interventions. In patients failing the non-invasive treatment approach, and who otherwise qualify for surgical intervention, two surgical approaches will be tested against a “*wait-and-see*” control group, with translaryngeal resistance measured before and after as an added numerical objective outcome measure.

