#### The CLE Scoring Procedure

Two highly experienced raters will score all CLE tests according to a system that has been published previously (18). EILO will be graded based on the severity of the visual obstruction of the supraglottic and glottic structures during exercise, with scores from 0 (complete patency) to 3 (almost complete closure) at the glottic and supraglottic level at moderate and at maximum intensity (Figure 3) (2, 18, 19). Both raters have assessed CLE recordings from ~3,000 individuals (18). The raters will review the video recordings retrospectively and not in the test situation, with recordings presented to each rater blinded to the identity of the patient and to whether the recordings were obtained before or after the intervention. Cases where scores differ between the two raters will be solved by consensus.

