#### Measuring Translaryngeal Resistance

Patients eligible for surgical intervention (Figure 2) will perform CLE tests that include also measurements of translaryngeal resistance, thus providing outcome measures not subject to any form of bias by the raters. The method has been described in a previous communication (21). Briefly, calculation of resistance is based on pressure recordings obtained from two pressure sensors placed above and below the larynx, and the airflow measured at the mouth. The vocal fold and proximal trachea will be anesthetized by lidocaine administered *via* an Olympus Spray tip catheter PW-6C-1 producing a lidocaine mist. Two pressure sensors (Mikro-Cath 825-0101, Milar, Houston, USA) will be introduced through a work channel in the laryngoscope, the first positioned approximately corresponding to the fifth tracheal ring and the second at the tip of the epiglottis. Both sensors are connected to a data acquisition box (Powerbox 8/35, AdiInstruments, Oxford, UK), collecting the data at 40 Hz, stored on a MacBook laptop using LabChart 8.0 software. Maximum inspiratory translaryngeal resistance will be determined at exhaustion; i.e., using ~10 breaths during the last 10 s of the CLE test, using this equation: [RL = PT – PE/AF] where RL is Laryngeal resistance (cm H_2_O/Ls-1), PT is Tracheal pressure reading (cm H_2_O), PE is Epiglottic pressure reading (cm H_2_O), AF is Airflow in Liters per second.

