### Statistical Model

The primary outcome is CLE score obtained close to peak exercise, measured on an ordinal 0–6 scale. For the main analysis, a proportional odds (cumulative logit) model will be fitted to the data. The explanatory variables will be the two treatment factors, their interaction and the baseline CLE score (as a continuous/linear variable). If the interaction is clearly insignificant, *P* ≥ 0.20, it will be removed from the model, and the results will be reported for the simplified model. The results will be presented as odds ratios (with the control arm as the reference group) with confidence intervals (CIs). Mean scores for the four arms will also be reported, with CIs calculated using the percentile bootstrap. If the baseline score is statistically significant (*P* ≤ 0.05), estimated model-based probabilities of obtaining the various CLE scores based on baseline CLE score and treatment arm will be reported.

A similar proportional odds model will be fitted for the surgical part of the study, the only difference being three instead of four treatment arms. With the relative small number of patients, there is a risk of non-convergence of the ordinal model (mainly if all patients in an arm end up with the same score). In this case, we will instead use a chi-squared omnibus test, followed by pairwise chi-squared tests. The *P*-values from these pairwise tests will be adjusted for multiple comparisons using Fisher's procedure (34).

There is uncertainty in how the proposed ordinal models will fit the data. We may need to do some adjustments to the model to improve model fit (e.g., include the baseline scores as a quadratic instead of a linear term), or possibly use other statistical models. If no statistical model can be found that adequately fits the data, we will simply report the score distribution in the four/three arms, along with mean scores and corresponding confidence intervals.

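### Phase 3 rests its analysis and power on a rater-judged CLE score that the protocol says cannot be blinded after surgery, while its scoring section claims blinding for all CLE tests

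*Protocol article*

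**What the plan says.** All places are in the protocol article.

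- **The CLE Scoring Procedure.** Two raters score all CLE tests from recordings, "blinded to the identity of the patient and to whether the recordings were obtained before or after the intervention". No phase is exempted.
- **EILO Diagnostic Methods and Graded Outcome Measures** (text after Figure 1). "As surgery leaves obvious marks in the larynx, blinding of raters will not be possible in research". The same paragraph gives this as the reason for wanting an objective resistance measure.
- **Statistical Model.** "The primary outcome is CLE score obtained close to peak exercise, measured on an ordinal 0–6 scale". For Phase 3: "A similar proportional odds model will be fitted for the surgical part of the study, the only difference being three instead of four treatment arms". The chi-squared fallback is also on the CLE score.
- **Power Analysis.** Phase 3 is sized on CLE scores only: 14 per arm, odds ratio 0.05, mean 3.18 without surgery against 2.17 with it, power about 98% overall, 89% pairwise and 90% for the fallback test.
- **The Specific Aim of This Study.** Phase 3 is run "with translaryngeal resistance measured before and after as an added numerical objective outcome measure".
- **Measuring Translaryngeal Resistance.** Resistance is measured in patients eligible for surgery, "thus providing outcome measures not subject to any form of bias by the raters". The Follow-Up section repeats the pressure measurement 2–4 months after surgery, and at the matching time in the no-surgery arm.
- **Supraglottoplasty—Minimally Invasive Procedure.** Arm F is said to leave the gross anatomy of the larynx unchanged; in arm E tissue is excised.

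**The concern.** Two statements about one property of the primary outcome contradict each other, and the contradiction falls on the comparison where blinding matters most. The introduction concedes that CLE rating has a subjective element. In Phase 3 that rating compares an irreversible operation with no operation, and a rater who sees surgical marks knows both that the recording is post-treatment and that the patient was operated on. Any expectation of benefit can then enter the score, and the planned test cannot tell it from a treatment effect.

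The loss of blinding may also be uneven. If the full procedure is easy to recognise and the minimally invasive one is not, the bias falls mainly on E, and the comparison of E with F is distorted as well.

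A reader of the scoring section alone would take the Phase 3 result to be blind-assessed.

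**Working it through.** **1. The plan's own figures.** Inputs from Power Analysis: no-surgery distribution of scores 2 to 6 of 23, 45, 25, 5 and 2%; odds ratio 0.05; 14 per arm. A two-sided 5% level is assumed.

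- No-surgery mean: 2(0.23) + 3(0.45) + 4(0.25) + 5(0.05) + 6(0.02) = 3.18.
- Surgery distribution: divide each cumulative odds by 0.05. For score 2: 0.23/0.77 = 0.299; 0.299/0.05 = 5.97; 5.97/6.97 = 0.857. Repeating this gives 85.7, 12.0, 1.9, 0.3 and 0.1%, mean 2.17, difference 1.01, as stated.
- Simulated power: overall 98.7% (proportional-odds likelihood ratio) and 98.3% (Kruskal-Wallis), against about 98% stated; chi-squared 90.2–90.7% against 90%; pairwise 90.6% (rank-sum, Bonferroni over three) against 89%.

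The stated power therefore reproduces. It assumes scores without rater bias and says nothing about detection bias.

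**2. How rater expectation would act (illustration).** Assume no true effect, so all three arms follow 23/45/25/5/2%. Among operated larynges that would score above 2, a share b is rated one grade lower; scores of 2 are left alone, since 2 is the lowest category in the plan's calculation. The documents give no value for b.

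- Share that can be lowered: 0.45 + 0.25 + 0.05 + 0.02 = 0.77.
- Share of all operated larynges lowered = 0.77 × b. Each moves one grade, so this is also the spurious difference in mean score.

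| b | 0.77 × b | Mean difference | False-positive rate, overall Kruskal-Wallis at 5% |
|---|---|---|---|
| 0 | 0 | 0 | about 5% |
| 10% | 7.7% | 0.08 | about 5–6% |
| 25% | 19% | 0.19 | about 8% |
| 50% | 39% | 0.39 | about 22% |
| 75% | 58% | 0.58 | about 46% |

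A proportional-odds likelihood-ratio test without baseline, closer to the planned model, gives a similar picture in 400 runs per case: about 6% with no bias, 5% at b = 10%, 11% at 20%, 13% at 30% and 25% at 50% (Monte Carlo error about 1–2 points).

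**3. If only arm E is recognisable.** The overall Kruskal-Wallis rates are nearly the same (about 8–9%, 21% and 45–46% at b = 25%, 50% and 75%), but the spurious difference now also lies between E and F.

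**4. The resistance formula.** It is printed as "RL = PT – PE/AF] where RL is Laryngeal resistance (cm H_2_O/Ls-1"). Read literally, it subtracts a pressure per flow from a pressure, which cannot have the stated unit. Pressure per flow requires (PT − PE)/AF. With assumed readings PT = −20 and PE = −2 cm H2O and flow 3 L/s, the literal reading gives −20 − (−2/3) = −19.3, and the bracketed one −18/3 = −6.0.

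**The case against.** **The limit is disclosed and partly met.** The article itself says raters cannot be blinded after surgery and measures resistance for that reason, in the control arm too. This stands. A reader might infer that a positive Phase 3 result could never be separated from rater expectation; the documents do not support that, because rater-independent data will sit beside the CLE scores.

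**CLE is a reasoned choice.** The article calls it the most objective severity measure to date, and calls resistance only promising, with feasibility reported in healthy volunteers and about 50 tests with pressure transducers so far. A reader might infer that resistance must replace CLE as the primary outcome. That does not follow: no variance, expected difference or repeatability is given for it, so a power calculation that reproduces would give way to unknown power.

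**A model for resistance may exist elsewhere.** The analysis of an added outcome is commonly left to the full protocol or SAP, which are not shown. Its absence from the article is not a fault.

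**Resistance is not free of all bias.** It is taken over the last 10 s of a test that ends at symptom-limiting distress or exhaustion. Patients who know whether they were operated on may differ in effort and flow.

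**The illustration is assumption-driven.** The values of b have no source, and even the largest spurious difference, 0.58, is below the postulated 1.01.

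**The formula is most likely a typographic slip.** The stated unit already implies the bracketed form. A reader might infer that resistance will be miscalculated; nothing in the article supports that.

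None of this reconciles the two blinding statements or changes the outcome on which Phase 3 is modelled and powered.

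**Conclusion.** The point holds in a limited form. The blinding statement in the scoring section is contradicted for Phase 3 by the article's own introduction, and CLE is the only outcome on which the article models and powers Phase 3. Surgery versus no surgery is therefore open to detection bias, possibly unequal between E and F. That inequality is an inference from the described anatomy, since the article's statement about surgical marks does not separate the two procedures.

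The size cannot be estimated from the documents. Under the assumptions above, the false-positive rate runs from near nominal at b = 10% to about 46% at b = 75%. These figures show sensitivity and are not a forecast. They come from an overall test without baseline adjustment.

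A reader might conclude that the Phase 3 power is wrong or that Phase 3 is uninterpretable. Neither follows: the power figures reproduce, and a safeguard is already being measured. The change should be made, but it concerns labelling and interpretation more than design.

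**What to change.** 1. In The CLE Scoring Procedure, limit the blinding statement to the non-invasive phases, and label Phase 3 CLE scores as unblinded there and in the report.
2. Pre-specify peak inspiratory translaryngeal resistance as a key rater-independent Phase 3 outcome, adjusted for its baseline value, for E versus G and F versus G.
3. State that a Phase 3 benefit on CLE will be interpreted together with the resistance result, and that unblinding may differ between E and F.
4. Minor: print the formula as (PT − PE)/AF.

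**Cost.** Wording in the protocol and SAP. No new measurement is needed, because resistance is already scheduled before and after in E, F and G. The price is in interpretation: the stated 98%, 89% and 90% apply to CLE only, power for resistance at 14 per arm is unknown, and resistance still depends on patient effort.

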### Treatment of EILO

The European Respiratory Society (ERS), the European Laryngological Society (ELS) and the American College of Chest Physicians (ACCP) joint Task Force Statement on EILO (13, 16) conclude the chapter on therapy by stating that future treatment studies must: “*Acknowledge the complex nature of laryngeal form and function, carefully categorise the patients by the new descriptive taxonomy, at least discriminate between laryngeal obstruction occurring at rest and during exercise, and whether glottic or supraglottic structures are primarily involved. Interventions and study outcomes must be clearly defined, and participants randomized into treatment and control arms.”*

Non-invasive treatments include strategies such as simple breathing advice, speech therapy (22, 23), biofeedback (24, 25), inspiratory muscle training (IMT) (10, 26), and laryngeal control therapy (23, 27). EILO subtypes are often not defined in studies, and the exact treatment methods are often poorly detailed. These issues complicate interpretations and question the generalizability of the findings (28). Our department has clinical experience with most types of treatment, in particular breathing advice, speech therapy, and IMT, as well as surgery offered to highly selected cases of motivated patients with significant supraglottic EILO, using laser supraglottoplasty.

### The Specific Aim of This Study

The specific aim of this study is to test the effect of four different non-invasive treatment approaches in a randomized controlled design in patients consecutively diagnosed with EILO at Haukeland University Hospital. Due to financial reasons, this is a one-center only study. Findings from continuous laryngoscopy performed during maximal treadmill exercise (CLE) will be used to diagnose and subtype EILO, and CLE-scores will be used to assess changes in the larynx at peak exercise before vs. after the interventions. In patients failing the non-invasive treatment approach, and who otherwise qualify for surgical intervention, two surgical approaches will be tested against a “*wait-and-see*” control group, with translaryngeal resistance measured before and after as an added numerical objective outcome measure.

## Methods

### Subjects and Design

The study will be conducted as a randomized controlled trial, performed at the EILO clinic at Haukeland University Hospital in Bergen, Norway, a nationwide referral center, annually seeing ~200 new patients. All study participants will be recruited from this EILO clinic. The design is outlined in Figure 2. After the diagnostic CLE test, all eligible patients will receive written information about the study. A nurse, not otherwise involved in the study, will provide oral information and be available for questions. Consenting participants will sign a written consent form before inclusion. For patients under the age of 16, their parents must also sign the form. Patients who decline participation will be offered treatment according to present department strategy; i.e., based on a “best practice” approach and according to current department policy for follow-up. We will need 140 patients in phase 1 and 30 patients in phase 3 (see statistics). However, our clinical experience is that ~10% of EILO patients are referred for surgery. The total number of included patients will then be 350.

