### Power Analysis

For practical reasons, we perform the power analysis for a simpler model, where the baseline score is not included. The distribution of CLE scores 2–6 for patients referred to our clinic and meeting the inclusion criteria has been searched in our EILO registry, and found to be 23, 45, 25, 5, and 2%, respectively. We expect that the control group will have a similar distribution, and use this as the basis for the power analysis. We postulate that one of the factors will be effective, with an odds ratio (OR) of 0.3, the other factor will have zero effect (OR = 0) and that there is no interaction. This corresponds to a reduction in mean CLE score of 0.53 for the effective treatment, from 3.18 to 2.65, and is both clinically relevant and in line with effect sizes observed in previous studies (10). The distribution of CLE scores 2–6 will then be 50, 38, 10, 2, and 1%, respectively. (We expect that in practice, some of the patients will have scores below 2, so 2 on this scale should be interpreted as ≤2.) With 35 patients in each arm, computer simulations show that this will give a power of 90% for an overall test of difference between the four arms (even when not using the rule about removing insignificant interactions). An alternative model, where the two treatments have the same effect (OR = 0.3) but there is no additional effect of having both treatments (i.e., a negative interaction) gives a power of 80%. In the actual study, we expect that the baseline score will be a good predictor of the outcome, which will further increase the power.

For the surgical part of the study, the power analysis is similar, with the “no surgery” arm having the same distribution of CLE scores as before (mean score 3.18). However, the effect of the two procedures is postulated as being much larger, OR = 0.05, which corresponds to a mean score in both surgery arms of 2.17. This difference in mean scores of 1.01 is in line with effect sizes from a previous study (11). Including 14 patients in each of the three groups will give a power of ~98% for an overall test (before any adjustment for the baseline scores), and 89% for pairwise comparisons (adjusted for multiple comparisons). The back-up chi-squared test will have a power of 90%. By clinical experience, surgical treatment is provided to ~14% of our EILO population, thus 42 patients entering Phase 3 is a reasonable estimate.

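### The article gives two Phase 3 sample sizes (30 and 42) and two surgery rates (~10% and ~14%), and no pairing of them yields the stated total of 350

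*Protocol article*

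**What the plan says.** Subjects and Design (Protocol article) sets the sample sizes and sends the reader to the statistics: "We will need 140 patients in phase 1 and 30 patients in phase 3 (see statistics"). It goes on: "However, our clinical experience is that ~10% of EILO patients are referred for surgery", and concludes: "The total number of included patients will then be 350".

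Power Analysis uses other figures for the same phase: "Including 14 patients in each of the three groups will give a power of ~98% for an overall test". It adds "89% for pairwise comparisons (adjusted for multiple comparisons") and "The back-up chi-squared test will have a power of 90"%. On feasibility it says that "surgical treatment is provided to ~14% of our EILO population, thus 42 patients entering Phase 3 is a reasonable estimate".

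Design and Randomization specifies equal allocation to the three surgical arms, so 30 patients means 10 per arm and 42 means 14 per arm.

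**The concern.** The first section cites the second as its source, yet the two disagree on both the number of patients and the surgery rate. The Phase 1 figure carries over correctly (4 × 35 = 140), so Subjects and Design is evidently meant to report the powered sizes. The total of 350 is presented as a consequence of the preceding figures but cannot be obtained from them.

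The Phase 3 number is the one that drives enrolment. Phase 1 needs 140 patients, who would supply only about 14 (at 10%) to 20 (at 14%) surgical candidates. The rest of the 350 is there to feed the surgical comparison. A reader cannot tell which Phase 3 size the trial is committed to, or whether the published power applies to it.

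**Working it through.** **1. Reproduce the plan's surgical effect.** Inputs from Power Analysis: control distribution of scores 2–6 of 23, 45, 25, 5 and 2%; OR 0.05 in both surgery arms.

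- Control mean: 2(0.23) + 3(0.45) + 4(0.25) + 5(0.05) + 6(0.02) = 3.18, as stated.
- With OR 0.05 for a higher score, the odds of scoring at or below each cut-point are multiplied by 1/0.05 = 20. For score ≤2: 0.23/0.77 = 0.299; × 20 = 5.97; probability 5.97/6.97 = 0.857. Repeating this at each cut-point gives 85.7, 12.0, 1.9, 0.3 and 0.1%.
- Surgical mean 2.17 and difference 1.01, both as stated.

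**2. Reproduce the stated power, then change only the arm size.** Three-arm multinomial data were simulated from these distributions without a baseline covariate, as in the plan. Tests: proportional-odds likelihood-ratio test on 2 df (overall), Pearson chi-squared (back-up), and likelihood-ratio tests of one surgery arm against control (pairwise). Two-sided alpha 0.05 is an assumption, because the power section states none. The ranges show the spread over repeated simulation runs.

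| Phase 3 total (per arm) | Overall | Back-up chi-squared | Pairwise, Bonferroni | Pairwise, Fisher protected |
|---|---|---|---|---|
| 42 (14/14/14) | 98–99% | 90% | 91–92% | 95–96% |
| 35 (12/12/11) | 96–97% | 82–85% | 87–89% | 93–95% |
| 30 (10/10/10) | 93–94% | 74–76% | 80–82% | 88–90% |
| *Stated in the plan* | *~98%* | *90%* | *89%, method not named* | |

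The overall and back-up figures are reproduced at 14 per arm. The stated 89% pairwise cannot be tied to one method. At 14 per arm, requiring both comparisons with control to succeed under Bonferroni gives 87%, so 89% lies within the 87–96% range across reasonable definitions. The published powers therefore belong to 42 patients; the article gives none for 30.

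**3. Derive the total.** Total = Phase 3 size / surgery rate.

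- 30 / 0.10 = 300
- 42 / 0.14 = 300
- 42 / 0.10 = 420
- 30 / 0.14 = 214

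None gives 350. In reverse, 350 × 0.10 = 35 and 350 × 0.14 = 49; 42/350 = 12.0% and 30/350 = 8.6%.

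**4. Chance that 350 supplies 42 candidates.** With X ~ Binomial(350, rate), P(X ≥ 42) is about 12% at 10% and about 88% at 14%. Both assume that every candidate agrees to be randomised.

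**5. Chance for totals without a margin.** By the same method, P(X ≥ 42) is about 53% for 300 patients at 14% and about 52% for 420 at 10%, because 42 is then only the expected number.

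**The case against.** The strongest reply is that this is a reporting slip with limited consequences.

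- **350 may contain a margin.** Both internally consistent pairs imply 300, so 350 is about 17% above that (350/300 = 1.167), and 42/350 = 12% lies between the two approximate rates. The total is therefore unexplained rather than shown to be too small. This stands. But no allowance is stated, losses are to be replaced rather than covered by inflation, and a margin would not reconcile 30 with 42.
- **The rates may measure different things.** One is the share referred for surgery and the other the share treated. The surgical section also says that in the trial the non-invasive pathway is stricter and availability does not limit surgery. Neither clinic rate is then an exact in-trial rate. This is fair, but the article uses each as the planning rate for the same phase.
- **Main-test power stays high.** Even at 30 patients it is about 93%, above the 90% planned for Phase 1 and before the baseline adjustment that the plan expects to help. The largest loss is in the back-up test, which is used only if the ordinal model fails to converge. This stands. The article does, however, link non-convergence to small numbers.
- **The pairwise loss depends on the method.** The drop to about 80% is a Bonferroni result. The only procedure the article names is Fisher's, for the back-up pairwise tests, and under it 10 per arm gives 88–90%, close to the stated 89%. This stands, so both figures must be shown.

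A reader might also infer that Phase 3 would be stopped at 30 patients and reported with power it lacked. The article contains no such stopping rule, so that inference is not supported.

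**Conclusion.** The contradiction is established from the printed figures alone: 30 against 42 patients, about 10% against about 14%, and a total that follows from no pairing. It is not an effect of condensing a longer protocol, since both sets of figures are printed and one cites the other.

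The published powers apply to 42 patients. At 30, the overall test loses about 5 percentage points (98% to 93%) and the back-up chi-squared test about 16 (90% to 74%). One comparison with control loses roughly 6 to 12 points, depending on the adjustment. These sizes rest on the plan's own distributions and OR, on two-sided alpha 0.05 and on no baseline covariate.

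It is tempting to conclude that the enrolment plan cannot deliver the stated power. The documents do not support that. With 350 included, the shortfall is likely if the rate is 10% and unlikely if it is 14%, and nothing in the article settles which is right. The inconsistency is unconditional; the shortfall is conditional.

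**What to change.** State one Phase 3 target and one surgery rate in both Subjects and Design and Power Analysis. Show how the total follows from them, with any allowance for refusal or loss made explicit, and give the power for that target, naming the pairwise adjustment and the alpha.

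- If 42 stands, correct the 30 in Subjects and Design and re-derive the total at the chosen rate with a stated margin.
- If 350 and about 10% stand, restate Phase 3 as about 35 patients, with power of about 96% overall and about 82–85% for the back-up chi-squared test.

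Do not substitute 300 or 420 as bare totals, since each reaches 42 candidates only about 52–53% of the time.

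The cost is two edited paragraphs and a rerun of the existing simulation. Some power figures may become less favourable, and the total may rise if the lower rate is kept with 42 patients.
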